#### Procedures

The dataset will be requested from NHS England once the necessary information governance and data sharing agreements are in place. NHS England will extract the requested data from the Mental Health Services Dataset. NHS England will remove any identifiable information from the dataset before it is transferred to the research team for analysis using Message Exchange for Social Care and Health (MESH), a secure system used by NHS England to transfer patient and service level data.

Component 4 is a service evaluation rather than a research study, using routinely collected data. Therefore, NHS ethics approval is not required.

#### Sample size

The Care Quality Commission (CQC) identified 4,400 inpatient rehabilitation beds in England in late 2018 [9]. Assuming a similar response rate to the GIRFT programme (85%), we can estimate that we will obtain data on 3,740 individuals. The sample size required for IVA depends on the strength of the instrument and the level of confounding. Our instrument (the extent to which each CCG ‘outsources’ inpatient rehabilitation to the independent sector) is likely to be a strong instrument i.e. a strong predictor of the receipt of inpatient rehabilitation in the NHS or independent sector (our main exposure variable). Using the same assumptions as in C3, a sample size of 350 participants is required to detect a difference of 0.38 SD in bed days (i.e. around 42 days, or 6 weeks) between NHS and independent sector rehabilitation units, using ordinary linear regression. A DE of 1.78 (based on an average cluster size of 14 and an intracluster correlation of 0.06 found in the REAL study) [4] is expected in C4 thus inflating this sample size to 623. Whilst the difference in the sample size required to perform an ordinary linear regression analysis and an IVA depends on the strength of the instrument and the unmeasured confounders, for a strong instrument and unmeasured confounders (our scenario), the sample size required for IVA and ordinary least square regression are similar [39]. Our estimated sample size of 3,740 is about 6 times the sample size required for a standard linear regression analysis and therefore should be adequate for the IVA.

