#### Sample size estimation

We aim to recruit 500 participants. A sample of 294 (half from NHS and half from independent sector units) will allow us to detect a mean difference in inpatient days of 0.38 SD (REAL study SD = 113, i.e. around 6 weeks) [7] between NHS and independent sector rehabilitation units, using a two-sample t test with 90% power and 5% significance level. Based on a bed day cost of £350, 6 weeks is an important difference, representing a potential saving of £14,700 per patient.

To perform the multivariable regression analysis described below, this sample size is increased to 350 after inflating, using a variance inflation factor (VIF) of 1.19 (derived using a multiple correlation coefficient of 0.16, the assumed proportion of variance in the service type explained by its association with the confounding variables). We do not have estimates available for the VIF from previous studies and thus assumed a moderate strength of association between service sector and the confounding variables [34]. The sample size further increases to 497 after allowing for a design effect (DE) of 1.42 (based on an average cluster size of 8 and an intracluster correlation of 0.06) [4].

Based on the REAL cohort study findings [7] and CQC report [9, 35], we estimate 160 NHS and 80 independent sector patient participants will be discharged during the 12 month recruitment period in C1 (without readmission) and around 33% NHS patients will be readmitted during follow-up. Thus, for our main secondary outcome, this sample size (240 patients) will allow us to detect a difference in readmission of 22.3% between NHS and independent sector units with 90% power or 19.7% with 80% power (based on a Z-test comparing two proportions) and 5% significance level assuming the same VIF and DE as above.

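### Component 4's case that 3,740 patients suffice for the instrumental variable analysis depends on an unstated first-stage R-squared; the six-fold margin is used up once that falls below about 0.14 to 0.17

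*Protocol article*

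**What the plan says.** The Component 4 sample size section of the protocol article carries over the Component 3 calculation: "a sample size of 350 participants is required to detect a difference of 0.38 SD in bed days", using ordinary linear regression. It applies a design effect, "A DE of 1.78 (based on an average cluster size of 14 and an intracluster correlation of 0.06 found in the REAL study"), to reach 623. It acknowledges that the IV requirement depends on instrument strength and confounding and says the instrument is likely to be strong. For that case it states that "the sample size required for IVA and ordinary least square regression are similar", citing a reference. The closing argument is "Our estimated sample size of 3,740 is about 6 times the sample size required for a standard linear regression analysis", from which it infers that the number is adequate for the IV analysis.

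The article gives no first-stage R-squared, correlation or F statistic and applies no inflation for instrument strength. The Component 4 analysis section makes the regression of bed days on the IV alone the main analysis, with covariates added only in sensitivity analysis.

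**The concern.** In large samples the variance of an IV estimate is about the ordinary least squares variance divided by the first-stage R-squared, that is, the share of the variance of sector explained by the instrument. This term usually dominates an IV sample size, and the plan leaves it out by treating the two methods as equivalent. A strong instrument in the usual sense, meaning a clearly significant first stage, does not bring the ratio near 1. Nor does the presence of unmeasured confounding.

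Component 4 is the part of the programme intended to cope with unmeasured confounding, and its bed-day data also feed the cost-efficiency analyses in Component 5. If its precision is overstated, readers cannot tell how wide a confidence interval to expect or how much weight a null result can bear.

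**Working it through.** **Inputs from the article.**
- Component 3, sample size estimation: "A sample of 294 (half from NHS and half from independent sector units"), "using a two-sample t test with 90% power and 5% significance level"; effect 0.38 SD with "REAL study SD = 113, i.e. around 6 weeks"; "this sample size is increased to 350 after inflating, using a variance inflation factor (VIF) of 1.19".
- Component 4, sample size: design effect 1.78; 4,400 beds; 85% response.
- Background: the independent sector provides around half the beds, so the proportion p in that sector is taken as 0.5.

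**Reproducing the plan's figures.** A two-sample t test at 0.38 SD, 90% power and two-sided 5% needs 146.5, so 147 per group, or 294. Then 294/(1 − 0.16) = 350; 1 + 13 × 0.06 = 1.78; 350 × 1.78 = 623; 0.85 × 4,400 = 3,740; 3,740/623 = 6.0. All stated figures reproduce. The effect in days is 0.38 × 113 = 42.9.

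**The missing step.** N_IV ≈ N_OLS / R².
- Break-even with the VIF: 623/3,740 = 0.167.
- Without the VIF, since the main IV model has no covariates: 294 × 1.78 = 523, and 523/3,740 = 0.14.

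**How large can R² be?** The instrument is constant within a CCG and the exposure is yes/no per patient, so R² is at most the between-CCG variance of the outsourcing share divided by p(1 − p) = 0.25.
- Uniform shares from 0 to 1: (1/12)/0.25 = 0.33.
- R² of 0.8 needs a between-CCG SD of √(0.8 × 0.25) = 0.447, against a maximum of 0.5. In a symmetric two-point pattern, every CCG would outsource about 5% or 95%.

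**Results with 3,740 patients.** The R² values are assumptions. Power = Φ(0.38 × √(3,740 R²/(VIF × 1.78))/2 − 1.96), with VIF 1.19 or 1. Detectable difference at 90% power = 42.94 × √(N_OLS/(3,740 R²)), with N_OLS 623 or 523.

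| R² | SD of CCG share | N needed (623/R²) | Power, with VIF | Days, with VIF | Power, no VIF | Days, no VIF |
|---|---|---|---|---|---|---|
| 0.05 | 0.11 | 12,460 | 43% | 78 | 50% | 72 |
| 0.10 | 0.16 | 6,230 | 71% | 55 | 79% | 51 |
| 0.167 | 0.20 | 3,740 | 90% | 43 | 94% | 39 |
| 0.25 | 0.25 | 2,492 | 98% | 35 | 99% | 32 |
| 0.33 | 0.29 | 1,888 | >99% | 31 | >99% | 28 |
| 0.80 | 0.45 | 779 | >99% | 20 | >99% | 18 |

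**Check by simulation.** The set-up was a binary exposure, a CCG-level instrument, 3,740 patients, an assumed 150 CCGs and no clustering of the outcome, with and without unmeasured confounding. The ratio of IV to ordinary-regression variance was about 10.8 at R² 0.10, 6.3 to 6.6 at 0.17, 2.8 at 0.33, 1.8 to 2.1 at 0.50 and 1.15 to 1.25 at 0.80. It follows 1/R².

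**Significance is not precision.** At R² = 0.05 the first-stage F is about 3,740 × 0.05/0.95 = 197, ignoring clustering, yet the IV analysis needs 20 times the ordinary-regression sample.

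**Design effect.** The intracluster correlation comes from a study of rehabilitation units, while the instrument varies only between CCGs. A larger design effect at CCG level would raise both break-even values in proportion.

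**The case against.** The sentence on similarity is conditional on a strong instrument, follows an acknowledgement that the requirement depends on strength, and cites a source that cannot be checked here. At R² of about 0.8 the ratio is only about 1.2, so a reader who concludes that the sentence is false outright goes too far. It is unsupported for this instrument rather than untrue in every case. This part of the objection stands.

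The six-fold figure is stated against standard linear regression and is right as such. It also works as a buffer: the conclusion of adequacy survives for any R² above break-even. The Background says use of the independent sector varied greatly by CCG, and the uniform case needs only about 1,890 patients. The uniform case is not a ceiling either, since CCGs clustered near none or all would exceed 0.33. This stands too, and it rules out the inference that Component 4 is underpowered.

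The 0.17 threshold carries a VIF that the main IV model does not need. Without it, a CCG-share SD of 0.20 (R² 0.16) needs 523/0.16 = 3,269, which is within 3,740. The threshold is therefore a range that depends on the design effect, not a fixed constant.

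Finally, the sample is everyone in a unit on a past census date, so the number cannot be changed, and a condensed article may leave the first-stage value to a fuller document. That would excuse a missing figure. It does not excuse the reason the article does give for adequacy, which transfers the ordinary-regression requirement to the IV analysis unchanged.

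**Conclusion.** The concern holds in a limited form. The stated basis for adequacy is unsound, because equivalence with ordinary regression needs a first-stage R² near 1, which a CCG-level share is unlikely to reach for a patient-level binary exposure. The claim that 3,740 give 90% power for 0.38 SD is true only if R² is at least about 0.14 (no VIF) to 0.17 (with VIF) under the stated design effect of 1.78.

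The documents give no R², so adequacy is not shown. A reader might infer from the lower rows of assumed R² that the study is too small, but those values are illustrations, and the only descriptive evidence, wide variation between CCGs, points towards a larger R². The result rests on the large-sample variance formula, p near 0.5 and the carried-over SD of 113 days.

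**What to change.** In the Component 4 sample size section:

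- Replace the sentence on similarity with N_IV ≈ N_OLS / R², where R² is that of the first stage.
- State that 3,740 patients give 90% power for 0.38 SD only if R² is at least about 0.14 to 0.17, according to whether the VIF is applied, under a design effect of 1.78. Say that a larger CCG-level design effect would raise this.
- Estimate R² from the between-CCG variation in the CQC data, which the opening of Component 4 says have already been shared, using the instrument as it is actually defined there.
- Restate the Component 4 detectable difference in days at that R².

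The cost is a few sentences and one variance calculation on data in hand. No one extra is enrolled and the analysis does not change. The stated margin will look smaller than six-fold.

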#### Analysis

Using appropriate regression models, we will estimate associations (1) between the IV and type of service received (NHS or independent sector) and (2) between the IV and successful rehabilitation. We will then investigate imbalance in key confounding factors (e.g. age, gender, latest HoNOS score) for the IV. The main analysis is a regression model using only the IV value as the predictor of outcome (total bed days over the 18 months follow-up). Then as part of the sensitivity analysis we shall rerun the regression analysis including key confounding variables that are potentially unbalanced in the regression model, in addition to the IV. As part of sensitivity analyses, different thresholds will be explored to construct the IV, based on the probability of CCGs outsourcing inpatient rehabilitation to the independent sector. Bias due to missing data will be investigated if applicable and sensitivity analyses under plausible missing data assumptions performed. Multiple imputation for missing data will be used if appropriate.

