#### Analysis

We will conduct two statistical analyses using the information collected from C1 and C3:

i.Multivariable regression

We will conduct linear regression using total inpatient days (since recruitment to C1) as our primary outcome and logistic regression using proportion of patients readmitted as our main secondary outcome, allowing for clustering within inpatient rehabilitation units. Service sector (independent or NHS) will be included in the model as the main explanatory variable. We shall adjust for relevant sociodemographic and clinical confounding variables, including inpatient days up to recruitment (gathered in C1), which may account for differences in outcomes between the two service types. We will use Directed Acyclic Graphs (DAGs) to ensure a logical and consistent approach to identifying potential confounders [36]. Suitable transformations will be used if assumptions of normality for linear regression are not satisfied. In addition, we will conduct exploratory analysis to investigate the relationship between the length of the inpatient rehabilitation admission (i.e. ‘dose’ of rehabilitation assessed in inpatient days), readmission and the service sector (independent or NHS), through a mediation analysis. Bias due to missing data in the explanatory variables (gathered in C1) will be investigated and we will use multiple imputation based on chained equations to impute missing values for these variables as appropriate.

ii.Multivariable regression with propensity score

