Anonymous patient identifier (linked to NHS number with key held by NHSE and not available to the research team).The CCG funding the inpatient rehabilitation admission.Baseline (i.e. census date: 1st February 2021) rehabilitation admission provider: NHS/Independent.Start date of the baseline rehabilitation admission.Start date of the baseline rehabilitation admission ‘spell’ (most inpatient rehabilitation patients are transferred from another inpatient ward; the ‘spell’ refers to the period when the patient was first admitted from the community to the point they are discharged to the community, including any transfers between inpatient wards).Gender at baseline.Age at baseline.Ethnicity.Rating of each Health of National Outcome Scale (HoNOS) item (12 in total) for HoNOS assessments recorded between the date 12 months before the census date (i.e. 1st February 2020) and the 18-month end date (i.e. 1st August 2022).HoNOS assessment dates.Inpatient service use during the cohort period (i.e. baseline date to 18-month end date).Discharged from the baseline inpatient rehabilitation admission: Yes/No.Date of discharge from the baseline rehabilitation service.Start and end date of any inpatient admission following discharge from the baseline rehabilitation admission, and the 18-month end date.

The 1st February 2021 was set as the census date in order that the 18 month study period (a) minimised the amount of time when Trusts were still affected by the COVID-19 pandemic and (b) avoided the impact of the cyber-attack of mid-August 2022 which affected several NHS Trusts. Trusts affected by the cyber-attack were unable to provide any data, including inpatient service use data, to NHS England for several months following the attack.

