We will conduct secondary cost-efficiency analyses [41] using the patient-level bed-day data collected in C1, C3 and C4, calculating the cost per patient and marginal cost per patient incurred over the study time period, according to their assigned inpatient rehabilitation group (NHS or independent sector). These analyses will use the same unit costs and cost perspective as for the cost-per-QALY analysis (see above), although the NHS cost perspective will be narrower as the C4 cohort will not have direct information on resources used beyond those reported in the Mental Health Services Data Set (MHSDS).

Adjustment covariates will include relevant sociodemographic and clinical confounding variables captured in C1 (for the main cost-utility analyses) or provided with the MHSDS (for the cost-efficiency bed-day analyses). Predictors of any missingness will be assessed and also included as adjustment covariates, and sensitivity analysis will assess the impact of uncertainty in assumptions and input parameters.

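### The main Component 4 model uses the instrument alone, so the headline result keeps any case-mix imbalance that the plan's own balance check finds

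*Protocol article*

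**What the plan says.** All references are to the protocol article; no SAP is shown.

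- **Component 4, Analysis** fixes the main model and its single predictor: "The main analysis is a regression model using only the IV value as the predictor of outcome (total bed days over the 18 months follow-up".
- The same section plans a balance check: "We will then investigate imbalance in key confounding factors (e.g. age, gender, latest HoNOS score) for the IV". It then says that "as part of the sensitivity analysis we shall rerun the regression analysis including key confounding variables that are potentially unbalanced". The check therefore decides which covariates go into the sensitivity model. It does not change the main model.
- **Component 4, list of requested variables**, shows what is available: "Gender at baseline.Age at baseline.Ethnicity", the 12 HoNOS items with their dates, and start dates for both the rehabilitation admission and the whole inpatient spell, where "the ‘spell’ refers to the period when the patient was first admitted from the community to the point they are discharged to the community".
- **Component 4, opening text**, justifies the instrument. It says outsourcing predicts the sector received and reaches the outcome by no other route, and likens the design to a randomised trial.
- **Component 3, Analysis**, adjusts its main model: "We shall adjust for relevant sociodemographic and clinical confounding variables, including inpatient days up to recruitment (gathered in C1". **Component 5, Analysis**, adjusts the bed-day cost analyses for covariates "provided with the MHSDS (for the cost-efficiency bed-day analyses".

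**The concern.** A regression with the instrument as sole predictor is unbiased only if the instrument is independent of case mix without conditioning on anything. How much a CCG outsources is a commissioning decision, not a random allocation, and the Background reports that it varied greatly between CCGs. The opening text of Component 4 at most asserts this independence, by saying that the instrument and outcome are linked only through sector. It offers no argument that CCGs which outsource more have similar patients. The planned balance check shows that the authors regard the matter as open.

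If the check finds a difference in, say, age or ethnicity, the main estimate still carries it. The correction appears only in a secondary model whose covariates were picked from the observed imbalance. That makes the secondary model data-driven, and it can leave out strong predictors of bed days that happen to look balanced.

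This is separate from whether the regression on the instrument is meant as a reduced form or as one stage of an IV estimate. A two-stage estimate without covariates would have the same weakness.

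**Working it through.** **The plan's own figures reproduce.**
- Two-sample t test, 0.38 SD, two-sided 5%, 90% power: 147 per group, 294 in total.
- VIF = 1/(1 − 0.16) = 1.19; 294 × 1.19 = 350.
- Component 4 design effect = 1 + (14 − 1) × 0.06 = 1.78; 350 × 1.78 = 623.
- Expected sample = 4,400 × 0.85 = 3,740, which is 6.0 times 623.
- Target = 0.38 × 113 = 42.9 days, given in the plan as around 42.

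The 350 already contains the VIF that Component 3 added for a covariate-adjusted regression. Without it the chain gives 294 × 1.78 = 523. Component 4 is thus sized with an allowance that its main model does not use.

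**Bias.** The SD of 113 is from Component 3, Sample size estimation. The other inputs are assumptions, because the documents give none: baseline imbalance between high- and low-outsourcing CCGs δ = 0.1 SD, covariate-outcome correlation ρ = 0.3 to 0.5, and difference in independent-sector use between those CCGs Δ = 0.30 to 0.50.

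Shift in the outcome contrast between the CCG groups = ρ × δ × 113, which is 3.4 days (ρ = 0.3) or 5.65 days (ρ = 0.5). Shift in the sector effect = that / Δ:

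| ρ | Δ = 0.50 | Δ = 0.30 |
|---|---|---|
| 0.3 | 6.8 days | 11.3 days |
| 0.5 | 11.3 days | 18.8 days |

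Against 42 days this is 16% (6.8/42) to 45% (18.8/42).

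**Simulation check**, with a continuous instrument: 267 clusters of 14, ICC 0.06, SD 113, true effect 42 days, first-stage slope 0.2 per SD of the instrument, instrument-covariate correlation 0.10, outcome slope 0.3 SD per SD. The formula predicts a shift of 113 × 0.3 × 0.10 / 0.2 = 17.0 days. The mean IV estimate was 59.6 days unadjusted and 42.1 adjusted. With zero instrument-covariate correlation the two were 41.5 and 41.4, so adjustment changes nothing when the instrument is balanced.

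**Precision.** Adjusted/unadjusted variance = (1 − R²_Y)/(1 − R²_Z), where R²_Y and R²_Z are the shares of outcome and instrument variance that the covariates explain.
- R²_Z = 0, ρ = 0.5: √0.75 = 0.866, intervals 13% narrower.
- R²_Z = 0, ρ = 0.3: √0.91 = 0.954, intervals 5% narrower.
- R²_Z = 0.16 (the plan's assumption for sector, not for the instrument) and R²_Y = 0.10: √(0.90/0.84) = 1.035, intervals about 3.5% wider.

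**Power.** Effective N = 3,740/1.78 = 2,101. With an assumed equal sector split, noncentrality = 0.38 × √(2,101/4 × first-stage R²), divided by √(1 − ρ²) after adjustment. With ρ = 0.5 and R²_Z near 0:

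| First-stage R² | Unadjusted | Adjusted |
|---|---|---|
| 0.05 | 0.495 | 0.614 |
| 0.10 | 0.786 | 0.889 |
| 0.15 | 0.921 | 0.973 |
| 0.30 | 0.998 | 1.000 |

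**The case against.** The strongest reply is that the plan already contains the remedy. It checks balance and reruns the model with covariates, so readers would see both results, and the dispute is only over which is called main. There is also a stated rationale: if the instrument mimics randomisation, an unadjusted main model followed by a balance check and an adjusted rerun is a coherent sequence. This stands in part. A reader might infer that Component 4 has no adjustment or no rationale, and the documents do not support either inference. What remains is that the headline is fixed as unadjusted whatever the check shows, and that the adjusted model is selected on observed imbalance.

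A reader might also infer that Component 4 contradicts Components 3 and 5. It does not. Both compare sectors directly, so adjustment is their main defence against confounding. They are weak precedents for an IV model. Research question 4, which asks for an adjusted comparison, is listed under Component 3.

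Nor do the documents support the reading that prior inpatient days and HoNOS plainly belong in the main model. The wait from spell start to rehabilitation start passes under the CCG's commissioning arrangements and may itself be affected by the instrument. The requested HoNOS window opens on 1 February 2020, so nobody admitted to the unit before then can have a pre-admission rating. The window also runs to the 18-month end date, so the latest score could postdate baseline. The plan's list of confounders is introduced as examples, so the absence of prior inpatient time from it is no omission; the full list may sit in the SAP.

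**Conclusion.** The point holds as a choice of main model that is worth changing. The headline Component 4 result retains any case-mix imbalance over an instrument that is not randomised, and the plan does not argue that the instrument is independent of case mix.

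The size cannot be derived from the documents. The illustrative shift of about 7 to 19 days, against a target of about 42, rests wholly on assumed imbalance, correlation and first-stage strength. If the instrument turns out balanced, the bias is nil.

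A reader might infer that the study is underpowered or clearly less precise as planned. That is not supported. Adjustment narrows intervals only if the covariates explain more of the outcome than of the instrument. The Component 4 Sample size section expects a strong instrument, and at a first-stage R² of 0.30 or more power exceeds 99% either way. The unused VIF allowance errs on the safe side for sample size. Adjusting for a few measured covariates also cannot prove that the instrument is valid; it removes only the measured part of the imbalance.

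**What to change.** In Component 4, Analysis:

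1. Make the main model adjust, in every stage, for a set of clearly exogenous baseline covariates already in the extract: age, gender and ethnicity. Fix the set in advance and do not select it from the balance check.
2. Report the IV-only model as the sensitivity analysis, and keep the balance check as a description.
3. Add inpatient days from spell start to rehabilitation start, and HoNOS limited to ratings on or before the census date, in labelled sensitivity models. Move either into the main set only if a DAG, a tool Component 3 already uses, supports treating it as unaffected by the instrument and by sector.

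The cost is a change of wording; no new data are needed. Some ethnicity values will probably be missing, for which the section already allows multiple imputation, and the main model becomes slightly less simple.

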## Methods

### Design

The ACER study is comprised of five Components:

a survey of NHS and independent sector inpatient mental health rehabilitation services across England to compare the quality of services and patient characteristics in the two sectors.a qualitative investigation of patient, family, staff and service commissioners’ experiences and perspectives on inpatient mental health rehabilitation provided by the two sectors.a cohort study comparing successful rehabilitation in the two sectors for the patients recruited in Component 1.a service evaluation retrospectively comparing successful rehabilitation over an 18-month period in the two sectors for all users of inpatient rehabilitation services in England on a specific census date, using instrumental variable analysis of routinely collected healthcare record data.a health economic evaluation calculating the relative cost effectiveness of inpatient rehabilitation services provided by the NHS and the independent sector using data from Components 1, 3 and 4.

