### Component 4: an instrumental variable analysis of NHS and independent sector inpatient mental health rehabilitation services using routinely collected healthcare records

In instrumental variable analysis (IVA), patients are not directly compared with respect to the treatments received. Rather, the approach compares groups who differ in their probability of receiving the treatments (in this case, receiving inpatient rehabilitation in the NHS or the independent sector). IVA is attractive since even in the presence of unmeasured confounding it may consistently estimate the average causal effect of an exposure on an outcome. It thus mimics the conditions of a randomised trial [38]. We plan to use the extent to which each CCG ‘outsources’ inpatient rehabilitation to the independent sector as an instrumental variable (IV), because it predicts receipt of inpatient rehabilitation in the NHS or independent sector (our main exposure) but has no direct effect on successful rehabilitation (our outcome). In other words, it is associated with successful rehabilitation only through its effect on the type of service received and has no indirect effect on the outcome via any other pathway. It thus meets the conditions required for an IV. The IV here is the proportion of inpatient rehabilitation beds each CCG commissions from the independent sector per 100,000 CCG population. The CQC have shared relevant data with us that will allow us to generate this variable for each CCG in England.

We will request NHS England to develop a dataset of all individuals in a mental health inpatient rehabilitation unit (NHS or independent sector) on 1st February 2021, the ‘census date’. This dataset will include all inpatient service use over the following 18 months (i.e. up until 1st August 2022) which will show whether the person has been discharged from the rehabilitation unit during this period or not, the date of discharge, and the admission and discharge dates of any subsequent inpatient admissions. The dataset will be comprised of the following variables:

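### The stated Component 4 main analysis regresses bed days on the instrument alone, so its coefficient is not the NHS versus independent sector difference that Component 4 sets out to estimate

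*Protocol article*

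**What the plan says.** The Design section describes C4 as "a service evaluation retrospectively comparing successful rehabilitation over an 18-month period in the two sectors for all users of inpatient rehabilitation services in England". The opening of the Component 4 section justifies the IV approach because "it may consistently estimate the average causal effect of an exposure on an outcome" even with unmeasured confounding, and it names sector of care as the exposure. The instrument is a CCG-level measure of independent sector commissioning, defined as a proportion of beds per 100,000 of CCG population.

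The C4 Analysis section says first that "we will estimate associations (1) between the IV and type of service received (NHS or independent sector) and (2) between the IV and successful rehabilitation". It then fixes the main model: "The main analysis is a regression model using only the IV value as the predictor of outcome", the outcome being total bed days over 18 months. In sensitivity analysis, "we shall rerun the regression analysis including key confounding variables that are potentially unbalanced in the regression model, in addition to the IV". A further sensitivity analysis varies the thresholds used to build the instrument.

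The C4 Sample size section takes 350 from Component 3 for a sector difference of 0.38 SD (about 42 days). It applies a design effect of 1.78, "based on an average cluster size of 14 and an intracluster correlation of 0.06 found in the REAL study", and reaches 623. It acknowledges that the IV sample size depends on instrument strength and calls the instrument strong. It says that in this setting "the sample size required for IVA and ordinary least square regression are similar", and concludes from a sixfold margin that 3,740 should be enough.

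**The concern.** An IV estimate of a sector effect has two ingredients: how the outcome moves with the instrument, and how sector of care moves with the instrument. The estimate is the first divided by the second, or its two-stage equivalent. The C4 plan obtains both ingredients but names the first, alone, as the main analysis. Sector received appears in none of the outcome models described.

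The headline C4 figure would therefore answer how bed days change as a CCG outsources more. It could not be set beside the Component 3 estimate or the six-week difference used for sizing. A reader who took it for the sector difference could be misled about how far the sectors differ, in a study meant to inform commissioners.

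The sample-size argument has a related gap. It moves from a regression on sector to an IV analysis on the strength of an instrument for which it gives no figure.

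**Working it through.** **1. The plan's own figures reproduce.**
- Two-sample t test, 0.38 SD, two-sided 5%, 90% power: 147 per group, 294 in total.
- Variance inflation factor (VIF): 1/(1 − 0.16) = 1.19; 294 × 1.19 = 350.
- Design effect: 1 + (14 − 1) × 0.06 = 1.78; 350 × 1.78 = 623.
- Expected patients: 4,400 × 0.85 = 3,740; 3,740/623 = 6.0.
- Target in days: 0.38 × 113 = 42.9, which the plan gives as about 42 days or six weeks.

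**2. What the stated main model estimates.** With a valid instrument and a common sector effect,

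reduced-form coefficient = sector effect × first-stage coefficient,

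where the first-stage coefficient is the change in independent sector use per unit of the instrument. The document gives no first-stage figure.
- On the per-100,000 scale, the coefficient is in days per unit of that scale. It has no fixed relation to 42 days in either direction.
- For a high/low instrument, the first-stage coefficient is the difference in independent sector use between high and low CCGs. Assuming 0.5: 42 × 0.5 = 21 days.
- Adding confounders or changing the threshold leaves the model in the same form.

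A simulation with assumed inputs (106 CCGs of 35 patients, instrument split at its median, true sector effect 43 days) gave a mean of 15.7 days for the regression on the instrument and 42.8 for the ratio estimate. The size of the dilution depends on those inputs.

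**3. What the sample-size statement needs.** In large samples the IV variance is the ordinary regression variance divided by the first-stage R², the share of variance in sector received that the instrument explains. So N_IV ≈ N_OLS / R².
- Break-even with the plan's 623: 623/3,740 = 0.167, a correlation of 0.41.
- The main C4 model has no covariates, so the VIF may not belong. Then 294 × 1.78 = 523 and 523/3,740 = 0.14, a correlation of 0.37.
- Assumed R² of 0.10, 0.20 or 0.30: 623/R² = 6,230, 3,115 or 2,077.

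**4. If clusters are larger than 14.** The instrument varies by CCG, and the level to which 14 refers is not stated. The cluster sizes below are assumptions; the intracluster correlation stays at 0.06.

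| Patients per cluster | Design effect | 350 × design effect | Minimum R² for 3,740 |
|---|---|---|---|
| 14 (plan) | 1.78 | 623 | 0.17 |
| 25 | 2.44 | 854 | 0.23 |
| 35 | 3.04 | 1,064 | 0.28 |
| 50 | 3.94 | 1,379 | 0.37 |

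**The case against.** The strongest reply is that the article names IV analysis as the method and plans the instrument-to-sector association, which is the missing denominator. On that view a statistician would take the ratio anyway, and the analysis plan may say so. The first half stands, and it makes the repair easy. The second does not settle the matter: the article states which model is the main one, so an analysis plan specifying two-stage least squares would contradict it, and one that followed it would not deliver the sector effect.

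Two further replies stand. With a valid instrument, the reduced form is a sound test of no sector effect, so the main test is not invalid. And dilution is not inevitable: if the instrument were simply each CCG's independent sector share from 0 to 1, the first-stage slope should be near 1 and the coefficient close to the sector effect.

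On sample size, the protocol admits the dependence on instrument strength, and its Background reports that use of the independent sector differs greatly between CCGs. If shares were spread evenly from 0 to 1 with slope 1 and half of patients in each sector (an assumption), R² would be (1/12)/0.25 = 0.33. That exceeds every break-even above except the one for clusters of 50.

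**Conclusion.** As written, no C4 outcome model yields an NHS versus independent sector difference in bed days, although the Design section, the Component 4 rationale and the sample-size section all make that the target. This follows from the text and needs no assumed figure. The size of the discrepancy does need assumptions: 42 days becoming 21 holds for a high/low instrument with a first-stage difference of 0.5.

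The sample-size limb is narrower. The arithmetic is right, but adequacy is asserted without a first-stage figure. It holds if R² is at least about 0.17 (0.14 without the VIF), or more if clusters exceed 14.

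A reader might infer four stronger things that the documents do not support:
- That the coefficient must be too small by a known factor. The instrument's scale and first-stage slope are not given.
- That 3,740 is too few. Nothing shows this.
- That the health economic evaluation inherits the problem. Its main analysis uses Components 1 and 3. From C4 it takes patient-level bed days by sector group, not the instrument coefficient.
- That clustering by unit, or intervals without clustering, is planned. The level behind the cluster size of 14 is not stated, a design effect is budgeted, and standard-error details may sit in the analysis plan.

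**What to change.** In the C4 Analysis section, define the main analysis as an IV estimate of the sector effect on total bed days. This can be two-stage least squares, or the ratio of association (2), taken on bed days, to association (1). Specify:
- the same covariates in both stages whenever the analysis is adjusted;
- intervals that respect the CCG level at which the instrument varies;
- reporting of first-stage strength (R² and F);
- the regression on the instrument alone kept as a supportive test.

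In the C4 Sample size section, replace the statement that the two sample sizes are similar with the relation N_IV ≈ N_OLS / R². State the first-stage R² assumed and the minimum at which 3,740 suffices, say at what level the cluster size of 14 applies, and say whether the VIF is retained.

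The cost is wording in two sections and no new data. Intervals for the sector effect will be wider than those for the reduced-form coefficient whenever the first-stage coefficient is below 1, but they will be on the scale the study needs.
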